### Eligibility criteria

2.4

Inclusion criteria:

Patients with chronic non-specific low back pain (pain or discomfort between the costal margins and inferior gluteal folds with or without referred pain to the lower limbs);Persistent low back pain for at least 3 months;^[23]^Pain intensity of at least 3 points, measured by Pain Numerical Rating Scale;^[24]^Aged between 18 and 65 years;Both genders.

Exclusion criteria:

Patients with severe skin diseases (e.g., skin cancer, erysipelas, severe eczema, severe dermatitis, severe psoriasis and severe hives lupus);Patients with low back pain associated with nerve root compromise (measured by clinical examination of dermatomes, myotomes and reflexes);^[25,26]^Serious spinal pathologies such as fractures, tumors, inflammatory and infectious diseases;Serious cardiovascular or metabolic disorders;Previous spinal surgery;Pregnancy.

### Procedures

2.5

The patients will be welcomed by the study's blinded assessor who will determine whether they will be eligible to participate in the study. Subsequently, a file will be completed with the patient's sociodemographic data and clinical history. Next, the primary and secondary outcomes of the study will be collected and all eligible patients will be randomized and allocated into 2 interventions groups: active PBMT or placebo PBMT. Fifteen minutes after the end of the single treatment session, the primary and secondary outcomes of the study will be collected again. The Consolidated Standards of Reporting Trials flowchart summarizing experimental procedures and patients is shown in Figure 1.

**Figure 1 F1:**
[figure not shown]
CONSORT flowchart.

### Randomization and blinding procedures

2.6

Prior to the single treatment session, patients will be randomized into their respective intervention groups: placebo or active PBMT. The randomization will be generated by a computer program (Excel Office 2010) and performed by a participating researcher not involved with the recruitment or evaluation of patients. This same researcher will be responsible for programming the PBMT device according to the result of the randomization (active or placebo mode) and will be instructed not to disclose the programmed intervention to the therapist, any of the patients or other researchers involved in the study until its completion. Concealed allocation will be achieved through the use of sequentially numbered, sealed and opaque envelopes. To ensure blinding for therapists and patients, the device will emit the same sounds and the same information on the display regardless of the programmed mode. Thus, patient and therapist will be blinded throughout the treatment.

### Interventions

2.7

Patients will undergo the treatment (active PBMT or placebo), according to prior randomization, in a single session:

1.Active PBMT: The PBMT will be performed using the Multi Radiance Medical Super Pulsed Laser MR4 console (Solon, OH), with the SE25 (emitter with an area of 4 cm^2^) and LaserShower (emitter with an area of 20 cm^2^) cluster probes as emitters. Nine sites will be irradiated on the patient's lumbar region: 3 central sites on top of the spinous processes (between T11 and T12, L2 and L3, L5 and S1), using the SE25; in the same direction, but laterally, 3 sites on the left and 3 on the right (on the paravertebral muscles), using the LaserShower (LS). PBMT irradiation sites and parameters were chosen based on a previous study.^[27]^ The treatment will be performed in a single session and the patients will receive a total dose of 220.05 J. Table 1 shows PBMT parameters.2.Placebo PBMT: Placebo PBMT will be delivered using the same device and the irradiated sites will be the same that active PBMT, but without any emission of therapeutic dose. Patients will receive a total dose of 0 J in placebo mode. The treatment will be performed in a single session.

**Table 1 T1:**
[figure not shown]
PBMT parameters.

### Outcomes

2.8

The primary outcome (levels of PGE_2_) and secondary outcomes (levels of TNF-α and IL-6 and pain intensity) of the study will be obtained at baseline and 15 minutes after the single treatment session by an assessor who will not be aware of patients’ allocation to their treatment groups:

Levels of TNF-α, IL-6 and PGE_2_ (inflammatory mediators): measured by enzyme-linked immunosorbent assay (ELISA) method. Blood samples (10 ml) will be collected by a qualified nurse (blinded to group allocation) and will be obtained from the antecubital vein. One hour after collection, each sample will be centrifuged at 3000 rpm for 20 minutes. Pipettes will be used to transfer the serum to Eppendorf tubes, which will be stored at −80°C until analysis. The levels of TNF-α, IL-6 and PGE_2_ in the blood samples will be determined by ELISA, using a commercial kit and following the manufacturer's instructions (BD Biosciences, USA). Spectrophotometric readings will be performed in a SpectraMax Plus 384 Absorbance Plate Reader (Sunnyvale, CA) with 450-nm wavelength and correction to 570 nm. The results of TNF-α and IL-6 will be expressed in pg/ml and the results of PGE_2_ will be expressed in pg/μl.Pain intensity: measured by the Pain Numerical Rating Scale.^[24]^ Pain Numerical Rating Scale evaluates pain intensity levels perceived by the patient on an 11-point scale ranging from 0 to 10, with 0 being ‘no pain’ and 10 ‘the worst possible pain.^[24]^ Patients will be instructed to score the level of pain intensity based at the time of evaluation.

### Statistical analysis

2.9

The statistical analysis will be conducted following the principles of intention-to-treat analysis.^[28]^ The findings will be tested for their normality using the Shapiro-Wilk test. Parametric data will be expressed as mean and standard deviation and non-parametric data as median and respective upper and lower limits. Parametric data will be analyzed by two-way repeated measures analysis of variance (ANOVA, time vs experimental group) with post-hoc Bonferroni correction. Non-parametric data will be analyzed using the Friedman test and, secondarily, the Wilcoxon signed-rank test.

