### Characterization of sample

2.3

Since no studies assessing the effects of PBMT on inflammatory mediators in patients with non-specific low back pain are available, the number of patients per group in the present study was calculated based on a pilot study. This pilot study was recently conducted by our research group with 3 patients per group in order to estimate the sample size. A β value of 20% and an α of 5% were used to calculate the sample size. The pilot study showed that applying PBMT in patients with non-specific low back pain resulted in levels of PGE_2_ (primary outcome of the present study) of 1.05 pg/μl (0.42 standard deviation), whereas applying the placebo in patients with non-specific low back pain resulted in levels of PGE_2_ of 1.52 pg/μl (0.39 standard deviation). We used the Researcher's Toolkit to calculate the sample size (https://www.dssresearch.com/resources/calculators/sample-size-calculator-average). Based on the aforementioned parameters used to calculate the sample, we found a sample of 9 patients per group, for a total of 18 patients. Since the phototherapy device used in the study causes no harmful thermal effects,^[22]^ patients of different skin colors will be recruited. The patients will be recruited through primary care doctors and physiotherapists.

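### A Shapiro-Wilk pre-test selects the primary PGE2 analysis, and only one of its two branches compares active with placebo

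*Protocol article*

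**What the plan says.** Section 2.9 (Statistical analysis) starts with the gate: "The findings will be tested for their normality using the Shapiro-Wilk test". Its result fixes the summary statistics ("Parametric data will be expressed as mean and standard deviation and non-parametric data as median and respective upper and lower limits") and then the test. On one side, "Parametric data will be analyzed by two-way repeated measures analysis of variance (ANOVA, time vs experimental group) with post-hoc Bonferroni correction". On the other, "Non-parametric data will be analyzed using the Friedman test and, secondarily, the Wilcoxon signed-rank test". No single primary method for PGE2 is named. The section gives neither the significance level of the pre-test nor what it is applied to: each arm-by-time cell, each arm, pooled values, change scores or residuals.

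Section 2.8 (Outcomes) says the outcomes "will be obtained at baseline and 15 minutes after the single treatment session", so each patient gives two values. Section 2.3 (Characterization of sample) sizes the trial on a difference between the active and placebo PGE2 means: "we found a sample of 9 patients per group, for a total of 18 patients".

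**The concern.** The trial is randomised and placebo-controlled, and it was sized on a difference between arms, so its primary question is active against placebo. The time-by-group term of the ANOVA answers that question. The fallback does not. Friedman and Wilcoxon signed-rank rank related measurements; with only a baseline and a 15-minute value they ask whether patients changed. Neither contains a term that sets one arm against the other.

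The pre-test therefore changes the hypothesis as well as the method, and it does so after the data are seen. A significant within-arm fall could be reported as the trial's result although regression to the mean, rest or a placebo response would produce the same fall in both arms. Outcomes in one report could also rest on different hypotheses, depending on which of them passed the pre-test. A gate with so much resting on it should be dependable, and at this sample size it is not.

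**Working it through.** **Inputs.** From section 2.3: pilot PGE2 of 1.05 (SD 0.42) pg/μl on active and 1.52 (SD 0.39) on placebo, 3 patients per group; 9 per group planned; "A β value of 20% and an α of 5% were used to calculate the sample size". From section 2.8: two time points. Assumed, because the protocol does not give them: lognormal shape, within-patient correlation 0.7, pre-test level 5%.

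**The plan's own figure.** Difference 1.52 − 1.05 = 0.47; pooled SD √[(0.42² + 0.39²)/2] = 0.405. With a one-sided 5% level, n = 2 × [0.405 × (1.645 + 0.842)/0.47]² = 9.19 per group, which is 9 if rounded down. With a two-sided level it is 11.67, so 12. Sidedness is a separate matter and nothing below depends on it. What matters here is that the figure rests on a between-arm difference.

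**Step 1: the two branches side by side.**
- ANOVA: with two time points, the time-by-group test is equivalent to a t-test comparing change between arms. It uses the randomisation.
- Friedman, then Wilcoxon signed-rank: each patient is a block with two values, and the tests ask whether the values shift within blocks. Run per arm or on all 18 patients, they give no active-versus-placebo comparison.

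**Step 2: how well the gate works.** Coefficients of variation (CV): 0.42/1.05 = 0.40 and 0.39/1.52 = 0.26. The lognormal log-SD is √ln(1 + CV²); at CV 0.40 it is 0.385. Shapiro-Wilk rejection rates at 5%, 5,000 samples per setting:

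| Data | 9 values | 18 values |
|---|---|---|
| Normal | 4.7% | 4.9% |
| Lognormal, CV 0.26 | 9.7% | 17.0% |
| Lognormal, CV 0.40 | 14.7% | 31.3% |
| Lognormal, CV 1.0 | 44.0% | 81.0% |
| Lognormal, CV 1.5 | 58.1% | 92.9% |

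Repeat runs differed by about a point, hence 9–15% and 17–32% at the pilot CVs. Monte Carlo standard error at 14.7% is √(0.147 × 0.853/5,000) = 0.5 points.

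**Step 3: how often normal data are diverted, if all four cells are tested.** For independent cells at exactly 5%, 1 − 0.95⁴ = 18.5%. Simulated with correlation 0.7 (4,000 runs): 17.5% for exactly normal data and 32% for lognormal data with CV 0.26.

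**Step 4: type I error.** For 9 per arm, correlation 0.7 and CVs from 0.26 to 1.0, the between-arm test on change rejects in 3.4% to 5.0% of runs with no true difference. The whole two-stage rule, with a Mann-Whitney test on change in place of the named fallback, rejects in 4.0% to 5.0%.

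**Step 5: what the named fallback can do.** Suppose PGE2 falls 20% in both arms (an assumption), four cells are tested, and the active-arm signed-rank result is read as the finding whenever the gate rejects. At CV 0.26 the gate rejects in 30.7% of runs, and the signed-rank test is significant in 77.3% of all runs. Treating these as independent, 0.307 × 0.773 + 0.693 × 0.050 = 27%, matching the simulated 27%. At CV 0.5 and 1.0 the simulated figures are 18% and 11%.

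**The case against.** The strongest reply is that a weak normality test does little harm in itself. When it misses skewness the data go to the ANOVA, which is the branch that does compare the arms, and step 4 shows that this branch is not anticonservative under skew. This stands. A reader might infer that pre-testing inflates type I error in general; the calculations do not support that. Had the fallback compared the arms, what remained would be a common practice with near-nominal error.

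Three other stronger readings also fail. First, that Shapiro-Wilk cannot detect skewness with 9 values: its power is low at the pilot CVs but 44–58% for strong skew, so it is unreliable, not blind. Second, that the method is chosen after unblinding: section 2.9 does not say when the pre-test is run, and both branches are written down in advance. What can be said is that the selection depends on the data. Third, that the gate often fires by chance: under normality that is 5% per test, and it reaches 17–18% only under the four-cell reading, which the protocol neither states nor excludes.

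The 11–27% in step 5 is an illustration. It needs a common fall in both arms and a within-arm test read as the result. It measures the defect of the fallback, not of pre-testing.

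The lack of a separate analysis plan does not answer the point, because section 2.9 states the switching rule and both branches outright.

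**Conclusion.** The point holds as a defect in what section 2.9 fixes. The data decide which of two hypotheses is tested for PGE2, and one of them leaves the randomised comparison untested. That conclusion follows from the text and needs no simulation.

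The size of the problem is conditional. The rejection rates at the pilot CVs assume lognormal data and rest on SDs from 3 patients per group. The share of normal datasets diverted depends on a testing unit that the protocol leaves open. Pooling to 18 values improves the gate but still leaves it missing at least two-thirds of such datasets. This should be changed before analysis; it does not show that the ANOVA branch would give a misleading result.

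**What to change.** Reword section 2.9, or settle it in the analysis plan before any outcome data are examined:

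- Delete the Shapiro-Wilk switch.
- Name one primary analysis for PGE2: ANCOVA of the 15-minute value on treatment group, adjusted for baseline, with the scale fixed in advance. The log scale is a reasonable choice for a positive concentration, though the documents do not dictate it.
- Add one rank-based or permutation test between arms as a sensitivity analysis.
- Use the same between-arm approach for TNF-α, IL-6 and pain intensity, with the scale fixed for each.
- Keep residual plots as a check that is reported, not as a rule that changes the method.

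No extra patients, visits or samples are needed. On the log scale the effect is a ratio rather than the pg/μl difference used in section 2.3. Baseline adjustment uses one degree of freedom, which is usually repaid. With equal variances, residual variance relative to a single measurement is 1 − ρ² for ANCOVA and 2(1 − ρ) for change scores; at the assumed ρ = 0.7 these are 0.51 and 0.60, a reduction of 15%.

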### Design

2.1

A two-arm, parallel randomized, triple-blinded (patients, therapists and outcome assessors), placebo-controlled trial will be performed. The protocol of this study has been prospectively registered on Clinicaltrials.gov (NCT03859505). The study will be conducted at Department of Global Public Health and Primary Care, University of Bergen, Norway.

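### For outcomes that fail the normality test, the plan names only within-patient tests, so active PBMT is never validly compared with placebo

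*Protocol article*

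**What the plan says.** Section 2.1 (Design) sets out independent arms: "A two-arm, parallel randomized, triple-blinded (patients, therapists and outcome assessors), placebo-controlled trial will be performed". Under section 2.8 (Outcomes), the primary outcome PGE2 and the secondary outcomes TNF-α, IL-6 and pain "will be obtained at baseline and 15 minutes after the single treatment session", which gives two values per patient.

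Section 2.9 (Statistical analysis) then sends each outcome down one of two routes. The selector is a pre-test: "The findings will be tested for their normality using the Shapiro-Wilk test". On the normal route, "Parametric data will be analyzed by two-way repeated measures analysis of variance (ANOVA, time vs experimental group) with post-hoc Bonferroni correction". On the other route, "Non-parametric data will be analyzed using the Friedman test and, secondarily, the Wilcoxon signed-rank test". No test for independent groups is named for non-normal data anywhere in the article.

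**The concern.** The two routes do not answer the same question. The ANOVA has an arm factor and an arm-by-time term, so it contains the randomised comparison. The Friedman and signed-rank tests have no arm term and require observations from the same patient or matched block. A preliminary normality test on a small sample therefore decides whether the placebo arm is used as a control at all.

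The rule covers every outcome, including the primary one. If an outcome takes the second route, the analyst has one within-arm result per group and will be drawn to contrast the two verdicts. Anything that moves both arms, such as a placebo response or an effect of repeat sampling, can then be reported as an effect of PBMT. For pain there is also regression to the mean, because patients enter on the same scale: "Pain intensity of at least 3 points, measured by Pain Numerical Rating Scale".

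**Working it through.** **1. The question the trial is sized for.** Section 2.3 compares PGE2 between arms: 1.05 (SD 0.42) on active and 1.52 (SD 0.39) on placebo, with α 5% and β 20%, giving 9 per group.
- Difference: 1.52 − 1.05 = 0.47. Pooled SD: √((0.42² + 0.39²)/2) = 0.405.
- n per arm = 2 × [SD × (z for α + z for power) / difference]².
- One-sided α: 2 × [0.405 × (1.645 + 0.842)/0.47]² = 9.19, which is 9 to the nearest integer.
- Two-sided α: 2 × [0.405 × (1.960 + 0.842)/0.47]² = 11.67, or 12.

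The stated 9 is thus close to a one-sided calculation, though the article does not give the sidedness. What matters here is that the sample size rests on active versus placebo, which the non-normal route never tests.

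**2. What the named tests can do in this design.**
- *Friedman within an arm.* With two time points the statistic reduces to (n₊ − n₋)²/n, where n₊ and n₋ count the patients who rose and fell. This is a sign test of post-treatment against baseline.
- *Signed-rank within an arm.* It also tests post-treatment against baseline. For n = 9, 10 of the 2⁹ = 512 sign patterns give W ≤ 5, so the two-sided p is 2 × 10/512 = 0.039. W ≤ 5 is the 5% critical region.
- *Friedman on four columns (2 arms × 2 times).* Each row must join an active patient to an unrelated placebo patient. The result depends on that pairing and responds to any time effect shared by both arms.
- *Signed-rank across arms.* It needs the same arbitrary pairing.

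**3. How often contrasting within-arm verdicts misleads.** Suppose both arms have the same true change, and each has probability π of a significant within-arm test. The arms are independent, so P(active significant, placebo not) = π(1 − π), and P(verdicts differ) is twice that. The maxima are 25% and 50%, at π = 0.5. With no common change and a symmetric distribution, π = 0.039 and π(1 − π) = 0.0375.

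Simulated results with 9 per arm, exact tests and no treatment effect (the common change and the distributions are assumptions):

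| Common change (SDs of change) | Normal changes: active only significant | Normal changes: verdicts differ | Skewed (lognormal) changes: active only significant | Skewed changes: Mann-Whitney between arms rejects |
|---|---|---|---|---|
| 0 | about 4% | about 7% (2 × 3.6%) | 6% | 4.1% |
| 0.25 | about 8% | about 16% (2 × 7.9%) | not run | not run |
| 0.5 | 17% | 34% | 14% | 4.3% |
| 0.75 | 25% | 49% | not run | not run |
| 0.8 | not run | not run | 23% | 3.9% |
| 1.0 | 21% | 43% | 8% | 3.8% |

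There were 40,000 trials per setting for normal changes and 4,000 for skewed changes. The formula agrees with the simulation: in the skewed run at 0.8 SD, π was 0.635, and 0.635 × 0.365 = 0.232 against 0.233 simulated.

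**4. Four-column Friedman, arms identical.** The shift here is in SDs of the outcome, and ρ is the baseline-to-post correlation. Rejection was about 4–6% with no shift, 14–29% at 0.5 SD, and 49%, 67% and 91% at 1 SD for ρ = 0, 0.5 and 0.8. The units differ from step 3: at ρ = 0.8 the SD of the change is √(2 × 0.2) = 0.63 outcome SDs, so a shift of 1 outcome SD is about 1.6 SDs of change.

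**5. Dependence on pairing.** In one simulated dataset, re-pairing the same patients at random moved the four-column Friedman p from 0.004 to 0.28 and the cross-arm signed-rank p from 0.13 to 1.0.

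**The case against.** The opposing case accepts the structural point and disputes its size and reach.

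- *The larger error rates need a shared change.* This is correct. With none, the misleading pattern appears in about 4% of trials, and four-column Friedman rejects at about its nominal level. The article gives no baseline-to-post change for either pilot arm, so a shift of 0.5–1.0 SD in PGE2 over so short an interval is an assumption.
- *The distribution matters.* Also correct. This route is for non-normal data, and at 1.0 SD the skewed run gives 8% against 21% for normal changes. The figures illustrate a range and do not predict a rate.
- *Regression to the mean concerns pain only.* Correct: entry is selected on pain and not on the mediators, and section 3 says the sample size was not powered with pain in view.
- *The defect is conditional.* It bites only if an outcome fails Shapiro-Wilk, and with 9 per arm that test has limited power. The article gives no distributions and states no rule for contrasting within-arm verdicts.

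These points limit the illustration. They do not supply a between-arm test where the plan has none. An unseen SAP does not answer the concern either, because the article goes beyond silence: it names particular tests, and they do not fit a parallel-group design.

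**Conclusion.** The concern holds. For any outcome sent down the non-normal route, the stated analysis contains no valid comparison of active with placebo, and this can include the primary outcome. That conclusion follows from the structure of the tests and needs no assumption about effect size or distribution.

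The practical size does rest on assumptions. If readers contrast the two within-arm results, the chance of an apparent active-only effect when the arms are identical runs from about 4% with no common change to about 25% at worst. Whether any outcome takes this route cannot be known from the article. The point must be fixed because the randomised comparison can be lost entirely and the correction is nearly free.

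**What to change.** Replace the sentence on non-normal data in section 2.9, and carry the change into the SAP, with a between-arm method fixed before unblinding. Suitable wording would be: outcomes not analysed by ANOVA are compared between arms by a Mann-Whitney (Wilcoxon rank-sum) test on the change from baseline to 15 minutes, with the Hodges-Lehmann difference and its 95% confidence interval; within-arm tests are descriptive only. A rank or permutation ANCOVA of the 15-minute value on baseline is an equally acceptable choice. What is essential is one pre-specified test of active against placebo.

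The cost is one sentence, with no extra data or patients needed to make the comparison valid. The change does not raise power. At the pilot means and SDs with 9 per arm and normal data, a Mann-Whitney test on the post-treatment level has about 57% power two-sided or 72% one-sided, against 64% and 76% for a t-test. That shortfall from 80% comes from the sample size, not from this correction.
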